**Costing of the HCV treatment:**

We will develop and pilot cost data collection tools that will allow us to perform a micro-costing of the investigated HCV treatment strategies. This method involves costing every input consumed in the treatment of a particular patient. Within our costing approach, we will also collect the costs incurred by patients and their families (such as their travel and food expenses). Using this wider, “societal”, perspective is becoming increasingly recognized as the gold standard for economic evaluations. This cost data will allow us to understand the costs of HCV treatment in Vietnam (for both the health system and the patients). This is also important for understanding potential barriers for receiving treatment.

The data will be collected based on the Hospital for Tropical Diseases electronic billing system, with additional questionnaires administered to the patients. It will be necessary to ask the patients and the informal caregivers basic demographical information (including questions regarding their salary and employment status), and the costs they incurred to travel to the clinic. This data will be collected using an outpatient costing questionnaire. This will be given to 20 patients from Stratum A and 20 from Stratum B. It will be administered three times to each patient (Stratum A timepoints: (D0, EOT (28/56), D84), Stratum B timepoints: (D0, D84, Week 12)). The patients will be selected randomly (and will not be given the economic burden questionnaire – to avoid repetition).

Based on the responses and data collected we will make improvements to the outpatient costing questionnaire. The finalized questionnaire will be used on a larger number of patients in the up-coming Wellcome trust HCV study. This will allow detailed and accurate cost data to be collected in a standardised manner which will be used to perform cost-effectiveness of different treatment strategies. An advantage of using this more detailed micro-costing approach is that it will allow us to investigate how the costs of providing HCV treatment could change if the coverage was scaled up, or if it was integrated into another control programme (such as those for HIV). This will help us to understand how generalizable our findings are to other low and middle-income settings.

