**STRATUM B (compensated cirrhosis, G6 HCV only, Response guided therapy)**

All participants will receive a minimum of 12 weeks of treatment. Those participants who have achieved virological suppression (VL <500IU/ml, as measured by Cobas assay, Roche) at the time of their D14 visit or sooner after treatment initiation will complete therapy at 12 weeks. Those who do not achieve virological suppression will continue to complete 24 weeks of therapy.

- 1. Protocol Treatment Discontinuation

In consenting to the trial, participants are consenting to trial treatment, trial follow-up and data collection.

Treatment (or retreatment) will be discontinued if any of the following occurs:

- toxicity which the investigator considers impedes the ability of the patient to continue intervention and/or the product information for the drug(s) contains a directive on discontinuation in the event of this specific toxicity
- participant requests for any reason to withdraw consent for treatment
- virological failure as defined above (move to retreatment if first-line failure and mild disease)

However, any such patient discontinuing study treatment (or retreatment) will be invited to continue follow-up “off study drug, on study” in order to obtain data on overall cure and adverse events. Participants should only discontinue study follow-up if they explicitly withdraw consent to continue to attend study visits. In this situation, participants may still contribute data collected at their routine clinic visits to the trial, providing they are willing to do so (“off study, follow-up through medical records only”).

1. Assessments & Follow-up
   1. Trial Assessment Schedule

See Appendix II, Trial Assessment Schedule.

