**Effectiveness of the HCV treatment**

Using established models describing the progressive stages of chronic HCV, we will aim to translate the outcomes of the trial into an estimated number of disability-adjusted life years (DALYs) averted. This will follow the approach used within the 2010 global burden of disease study. In addition, we will aim to administer the EQ5D-3L quality of life questionnaire to all of the enrolled patients at baseline (before treatment), midway during treatment, and after treatment (at the EOT+12 week visit). This data will allow us to measure the number of quality-adjusted life-years (QALY) saved due to the therapy.

1. Regulatory & Ethical considerations

All regulatory requirements (including safety reporting, see Section 8 - Safety Reporting and below) will be met by the sponsor or their delegated authorities.

- 1. Compliance

The trial will end at the final first-line or re-treatment EOT+12 week visit of all enrolled participants. Because the trial may contain a re-treatment phase, this may not necessarily be the final EOT+12 week visit of the last enrolled patient.

- - 1. **Regulatory Compliance**

The trial complies with the principles of the Declaration of Helsinki (2008) and will be conducted in compliance with the approved protocol and the principles of Good Clinical Practice (GCP).

- - 1. **SITE COMPLIANCE**

All sites will comply with the above. An agreement will be in place between the site and OUCRU, setting out respective roles and responsibilities.

The site will inform the OUCRU CTU as soon as they are aware of a possible serious breach of compliance. For the purposes of this regulation, a 'serious breach' is one that is likely to affect to a significant degree:

- The safety or physical or mental integrity of the subjects in the trial, or
- The scientific value of the trial
  1. Ethical Conduct of the Study
     1. **Ethical Considerations**

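### The Stratum B costing questionnaire is planned three times, but D84 and Week 12 counted from D0 are the same day, and no timepoint follows the end of a 24-week course

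*Protocol*

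**What the plan says.** Section 12.2 (Health Economics, costing of the HCV treatment) describes an outpatient costing questionnaire. On sample: "This will be given to 20 patients from Stratum A and 20 from Stratum B". On frequency: "It will be administered three times to each patient". The two schedules are "Stratum A timepoints: (D0, EOT (28/56), D84" for Stratum A and "Stratum B timepoints: (D0, D84, Week 12" for Stratum B. No origin is given for Week 12.

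The questionnaire is not the only cost source: "The data will be collected based on the Hospital for Tropical Diseases electronic billing system, with additional questionnaires administered to the patients". Among the items it covers are "the costs they incurred to travel to the clinic. This data will be collected using an outpatient costing questionnaire".

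Section 5.1 sets the Stratum B course: "All participants will receive a minimum of 12 weeks of treatment", extended to 24 weeks for those without the required day-14 response. Section 6.1 follows everyone for 12 weeks after treatment ends. Also in section 12.2, the last EQ-5D is placed "after treatment (at the EOT+12 week visit", so its origin is explicit.

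**The concern.** The schedule promises three occasions and, read as printed, names two days. Site staff cannot carry it out without guessing what the third entry means. If they take it literally, the questionnaire gathers nothing after treatment from participants on 12 weeks, and nothing from the second half of treatment or from follow-up in participants on 24 weeks.

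There is a second, smaller problem that does not depend on how Week 12 is read. Stratum A's middle occasion is tied to EOT and moves with the participant's course (day 28 or day 56). Stratum B's is fixed at D84, which is EOT only for the shorter of its two courses. What is at stake is the patient-cost part of the micro-costing, in a pilot whose finished tool is to be used in a larger study.

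**Working it through.** **Inputs**
- Three administrations per participant, 20 participants in Stratum B, days D0, D84 and Week 12 (section 12.2).
- Stratum B treatment of 12 or 24 weeks (section 5.1).
- Follow-up of 12 weeks after EOT (section 6.1).
- 90% of Stratum B expected to receive the shorter course (section 9.1).

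**Planned number**
20 × 3 = 60 questionnaires in Stratum B.

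**Reading (a): Week 12 counted from D0**
- 12 × 7 = 84, so Week 12 = D84. The distinct days are {0, 84}.
- Distinct occasions: 20 × 2 = 40, which does not reproduce the planned 60.
- 12-week course: EOT is day 84 and the final visit is day 84 + 84 = 168. The last questionnaire is at EOT, and the 84 days of follow-up come after it.
- 24-week course: EOT is day 168 and the final visit is day 168 + 84 = 252. The last questionnaire is mid-treatment; 168 − 84 = 84 days of treatment and a further 84 days of follow-up come after it.

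**Reading (b): Week 12 means EOT + 12 weeks**
- 12-week course: days {0, 84, 168}, that is baseline, EOT and final visit.
- 24-week course: days {0, 84, 252}. Day 84 is mid-treatment, EOT at day 168 has no questionnaire, and 252 − 84 = 168 days separate the second and third.
- Three occasions in both cases, so 20 × 3 = 60 is reproduced.

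**How many participants the second problem reaches**
- Expected on 24 weeks: 20 × (1 − 0.90) = 2.
- Chance of at least one: 1 − 0.90^20 = 1 − 0.12 = 0.88.

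**Stratum A for comparison**
The days are {0, 28, 84} or {0, 56, 84}: three distinct days on either course, with the second at the actual EOT. The last falls (84 − 28)/7 = 8 or (84 − 56)/7 = 4 weeks after EOT.

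**The case against.** The best defence is that reading (b) was intended. Much of the protocol labels on-treatment visits by day and post-treatment visits by weeks after EOT, so a list that switches from D84 to Week 12 fits baseline, end of the 12-week course, and the week-12 follow-up visit. That matches the promise of three administrations and the shape of the Stratum A list. The visit tables in Appendix II might settle it, but they are not legible in the copy reviewed. This stands as far as it goes: reading (b) is plausible and cannot be excluded. It is not what the text says, however. Elsewhere the protocol names the final visit with the EOT prefix, and here it does not. Nor does reading (b) supply an EOT questionnaire for a 24-week course.

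Three stronger conclusions are tempting, and the protocol does not support them.
- A reader might infer that no costs at all are captured after day 84. Billing data are a separate source, and nothing in the text limits them to day 84.
- A reader might turn the time after the last questionnaire under reading (a) into a share of cost lost: 84 of 168 days (50%) or 168 of 252 days (67%). Those shares hold only on that reading and assume that each questionnaire covers the whole preceding interval. No recall period is stated, and travel cost per visit can be multiplied by the number of visits. Understated costs are therefore not shown.
- A reader might infer that Stratum A and Stratum B costs can no longer be compared. The section plans no such comparison in these 40 participants.

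**Conclusion.** The point holds as an internal inconsistency with small reach. As printed, the Stratum B schedule gives two distinct occasions where three are promised, and none after a 12-week course. If Week 12 means EOT + 12 weeks, the count is right, but about 2 of 20 participants would be expected to have no questionnaire at EOT. That figure assumes that the 20 are representative of Stratum B and that the protocol's 90% is correct.

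The effect is limited to patient-reported costs from one questionnaire in an ancillary pilot reported separately from the main trial. It does not touch SVR12, the sample size or the safety analysis. No fault is shown in Stratum A's use of D84. It is a minor point, worth correcting because the schedule cannot be followed without interpretation.

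**What to change.** In section 12.2, restate the Stratum B timepoints as D0, EOT (week 12 or week 24, according to the participant's actual course) and the EOT+12 week visit. For a 12-week course this gives days 0, 84 and 168; for a 24-week course, days 0, 168 and 252. Make any matching entry in the Appendix II schedule and the CRF agree. Leave Stratum A as it is.

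The cost is one line of text. The total remains 60 questionnaires in Stratum B. Section 5 already schedules assessments at study entry, at end of treatment and 12 weeks later, so no visit is added. Participants on 24 weeks would no longer have a mid-treatment questionnaire at D84.

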**Effectiveness of the HCV treatment**

Using established models describing the progressive stages of chronic HCV, we will aim to translate the outcomes of the trial into an estimated number of disability-adjusted life years (DALYs) averted. This will follow the approach used within the 2010 global burden of disease study. In addition, we will aim to administer the EQ5D-3L quality of life questionnaire to all of the enrolled patients at baseline (before treatment), midway during treatment, and after treatment (at the EOT+12 week visit). This data will allow us to measure the number of quality-adjusted life-years (QALY) saved due to the therapy.

1. Regulatory & Ethical considerations

All regulatory requirements (including safety reporting, see Section 8 - Safety Reporting and below) will be met by the sponsor or their delegated authorities.

- 1. Compliance

The trial will end at the final first-line or re-treatment EOT+12 week visit of all enrolled participants. Because the trial may contain a re-treatment phase, this may not necessarily be the final EOT+12 week visit of the last enrolled patient.

- - 1. **Regulatory Compliance**

The trial complies with the principles of the Declaration of Helsinki (2008) and will be conducted in compliance with the approved protocol and the principles of Good Clinical Practice (GCP).

- - 1. **SITE COMPLIANCE**

All sites will comply with the above. An agreement will be in place between the site and OUCRU, setting out respective roles and responsibilities.

The site will inform the OUCRU CTU as soon as they are aware of a possible serious breach of compliance. For the purposes of this regulation, a 'serious breach' is one that is likely to affect to a significant degree:

- The safety or physical or mental integrity of the subjects in the trial, or
- The scientific value of the trial
  1. Ethical Conduct of the Study
     1. **Ethical Considerations**

The primary benefit of participation for individual patients in this trial is that >90% of individuals will achieve cure of hepatitis C without interferon-based treatment within the protocol. For many, interferon will have been a barrier to accessing and/or adhering to treatment previously. Barriers to accessing treatment are likely to remain even with increasing availability of directly acting antivirals (DAAs), as demand for treatment is expected to exceed the capacity to deliver it in setting such as Vietnam. The primary outcome measure (sustained virological response 12 weeks after end of treatment, SVR12) has been associated with significant reductions in all-cause mortality, cirrhosis and liver cancer [[18](#_ENREF_18)], and so achieving cure will significantly reduce individual patient’s future risks of these events. The study will use licensed medications that have been recommended as part of the WHO Essential Medicines list since 2015.

For the majority of participants, it is expected that cure can be achieved with a shorter duration of therapy than they would have received through routine care. The main risk in participation is that short-course therapy will not lead to SVR12/cure and there is a theoretical possibility that participants may develop viral resistance perhaps compromising future treatment options. However, emerging data in this area [[15](#_ENREF_15)] [[23](#_ENREF_23), [24](#_ENREF_24)] are reassuring in that, even with emergence of NS5A mutations, cure rates of >90% can be achieved with retreatment. On this basis approval has been given to previous studies of shortened treatment courses (e.g. STOPHCV-1). As recommended in a recent review, all those not cured initally will be routinely retreated for 12 weeks [[25](#_ENREF_25)]. Even assuming conservative estimates of retreatment success, >90% of those included in study should achieve SVR12.

The intervention agents used within this trial have already completed Phase III trials (ALLY studies) and have been approved for use by regulatory bodies including FDA, EMA, NICE and WHO. There are data on adverse event profiles from over 300 individuals with daclatasvir [[26](#_ENREF_26)] and >10,000 participants treated with sofosbuvir [[27](#_ENREF_27)]. Of the intervention treatments in this study and no major safety/toxicity concerns have yet emerged; as such, given the future mortality and morbidity, the potential for cure outweighs the risks of treatment for individuals. Because these medications are now being rolled out more widely, it is possible that new evidence of toxicity will emerge, but given that treatment has a finite duration, and the trial will test response guided shortened courses, the likelihood of new toxicities emerging to place individual participants at unacceptable risk is low.

Societal benefits arising from understanding which individuals can be cured with shortened therapy are potentially substantial. The treatment interventions within this study are currently priced at a level where access will not be affordable for all infected participants, many of whom are likely to need to self-fund treatment, at least in part. The findings from this study will inform how health services can efficiently provide treatment to those with mild disease, avoid over-treating many participants and allow more participants to be cured within a finite resource. Furthermore, the findings will inform the more precise use of new treatments in participants for whom a shortened 12 week course of therapy will still be challenging and will inform strategies that will allow individuals who may be cured with as little as 4 weeks of treatment to be identified.

- - 1. **Ethical Approvals**

The trial will be approved by the Imperial Research Ethics Committee, Oxford Tropical Research Ethics Committee, the Ethics Committee of the Hospital for Tropical Diseases and the Vietnam Ministry of Health. Regulatory approval will be given by the Drug Administration of Vietnam (DAV).

Any amendments will be submitted and approved by these ethics committees.

- - 1. **Confidentiality**

The investigator must assure that participants’ anonymity will be maintained and that their identities are protected from unauthorised parties. Participants will be assigned a trial identification number and this will be used on CRFs; participants will not be identified by their name. The investigator will keep securely a participant trial register showing identification numbers, surnames and date of birth. This unique trial number will identify all laboratory specimens, case record forms, and other records and no names will be used, in order to maintain confidentiality.

- - 1. **Expenses**

The study funding will cover the following costs:

- Study specific screening tests and procedures.
- Study related diagnostic, treatment and hospital costs from enrolment to the final study visit at EOT+12 weeks (including re-treatment for any participants in the mild disease cohort failing first-line treatment).
- Hospital costs (including costs of hospital accomodation, related investigations, and treatment), for participants admitted for adverse events
- Treatment of any adverse events which are caused by study participation.
- Travel expenses for the patient to attend follow-up visits (based on actual costs at standard OUCRU rates).

The details of the costs covered by the trial will be set out in the contract between OUCRU and the study site, but will follow the principles described above.

1. Oversight & Trial Committees
   1. Trial Management GROUP (TMG)

A Trial Management Group (TMG) will be formed to conduct the day-to-day management of the trial at the OUCRU CTU. This will include the Chief Investigator, Site PI, Trial Statistician, Clinical Project Manager, Trial Manager, Lab Manager and Data Manager. The group will meet at least once per month, although may meet more or less often as required. The group will discuss issues related to the progress of the trial at the site and to ensure that the trial is running well.

The full details can be found in the TMG Charter.

- 1. Data Monitoring Committee (DMC)

An independent Data Monitoring Committee (DMC) will oversee the safety of the trial. The DMC will review the confidential, accumulating data for the trial separately by treatment group. A DMC Charter will be drawn up that describes the membership of the DMC, relationships with other committees, terms of reference, decision-making processes, and the approximate timing and frequency of any interim analyses.

See Appendix I - Data Monitoring Committee Membership for membership.

1. Finance and insurance

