Cure is defined using the LLOQ, <15 IU/ml, 12 weeks after end of treatment (EOT). However, failure before this timepoint is defined using a slightly higher threshold because patients have been observed to achieve cure despite having low-level viraemia at the EOT or shortly after, and so they do not need re-treatment to achieve cure. In practice any patient with low-level viraemia <2000 IU/ml either cures or viral load rises above this level. This will be carefully reviewed by the Data Monitoring Committee. This is the same definition as used in the UK STOP-HCV-1 trial ISRCTN 37915093), where the Data Monitoring Committee has similarly reviewed individual patient viral load trajectories and has not raised any concerns.

Secondary endpoints

Secondary endpoints for the trial are

- SVR12 after the end of the combined first and any re-treatment phases (mild patients only)
- lack of initial virological response (<1 log_10_ decrease in HCV viral load from baseline)
- serious adverse events
- grade 3/4 clinical adverse events
- adverse events of any grade leading to change in treatment (SOF, DCV or any other medication)
- adverse reactions (any grade) (considered definitely/probably/possibly related to SOF or DCV)

1. Participant identification

There will be no exceptions to eligibility requirements at the time of recruitment. Questions about eligibility criteria should be addressed prior to attempting to enrol the patient – clarifications may be sought from the trial team.

The eligibility criteria are the standards used to ensure that only medically appropriate participants are considered for this study. Participants not meeting the criteria should not join the study. For the safety of the participants, as well as to ensure that the results of this study can be useful for making treatment decisions regarding other participants with similar diseases, it is important that no exceptions be made to these criteria for admission to the study.

Participants will be considered eligible for enrolment in this trial if they fulfil all the inclusion criteria and none of the exclusion criteria as defined below.

Recruitment will take place from clinics within the Hospital for Tropical Diseases in Ho Chi Minh City.

- 1. Inclusion Criteria

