The site PI or an appropriately trained doctor must seek written informed consent from patients to enter into the trial in their own language. Individuals trained and responsible for taking consent will be documented on the trial’s Delegation Log (with signatures). Consent will be sought after explanation of the aims, methods, benefits and potential hazards of the trial and BEFORE any trial-specific procedures are performed or any blood is taken for the trial, including for the screening assessment.

The doctor taking consent must make it completely and unambiguously clear that the participant is free to refuse to participate in or withdraw from all or any aspects of the trial, at any time and for any reason, without incurring any penalty or affecting their subsequent treatment. This will be stated explicitly in the participant information sheet.

Signed consent forms must be kept by the investigator and documented in the case record form (CRF) and a copy given to the participant.

- 1. Co-enrolment Guidelines

Treatment with any other investigational product within 60 days prior to screening is an exclusion criteria, and therefore co-enrolment with a previous investigational medicinal product (IMP) trial will generally not be allowed, unless the patient is in a follow-up phase. Before enrolment into the study of a patient already participating in a previous trial (not of an investigational product), the site investigator must confirm with the investigators of the previous trial that co-enrolment is allowed. Co-enrolment in the study of patients already participating in an observational study is allowed.

1. TReatment of PARTICIPANTS

Each participant will be treated with the same drug combination (sofosbuvir 400mg and daclatasvir 60mg daily), but with differing durations of therapy. The study design is open-label; bias will be minimised by using objective laboratory measurements to determine duration of therapy and to assess treatment outcomes .

Any patient in the mild disease cohort who experiences failure of first-line treatment will initiate re-treatment as soon as possible after failure is identified. Failure of first-line treatment during the study is defined as

1. two consecutive measurements of HCV RNA > LLOQ (taken at least one week apart) after two consecutive visits with HCV RNA <LLOQ, at any time during the study follow-up period, with the latter confirmatory measurement also being >2000 IU/ml OR

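### Section 13.2.1 says everyone not cured will be re-treated and rests a >90% cure statement on it, but the rest of the protocol provides re-treatment for mild disease only

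*Protocol*

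**What the plan says.** Section 13.2.1 (Ethical Considerations) opens with the benefit to individuals: ">90% of individuals will achieve cure of hepatitis C without interferon-based treatment within the protocol". The same sentence appears in section 1, under risks and benefits. Section 13.2.1 then names failure of short-course therapy as the main risk of taking part. It replies that "all those not cured initally will be routinely retreated for 12 weeks" and concludes: "Even assuming conservative estimates of retreatment success, >90% of those included in study should achieve SVR12". Neither of these two sentences is limited to a stratum.

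The operative sections are limited:

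- Section 5: "Any patient in the mild disease cohort who experiences failure of first-line treatment will initiate re-treatment as soon as possible after failure is identified".
- Section 5.1 gives re-treatment eligibility in the Stratum A text. The Stratum B text has no such provision.
- Section 5.2, among the reasons for stopping treatment: "virological failure as defined above (move to retreatment if first-line failure and mild disease".
- Section 6.2 refers to moving to re-treatment for the mild disease cohort.
- Section 13.2.4, on the costs the study covers: "including re-treatment for any participants in the mild disease cohort failing first-line treatment".
- Section 2.2, secondary endpoints, repeated in the trial summary: "SVR12 after the end of the combined first and any re-treatment phases (mild patients only".
- Appendix II has a re-treatment schedule heading for Stratum A and none for Stratum B.

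**The concern.** The protocol gives two different rules on what happens to a participant with cirrhosis whose first-line treatment fails. One, in the section ethics committees read for the balance of benefit and risk, says the participant is re-treated. The other, in every section that governs conduct, provides nothing within the study. Section 7.9.1 leaves later treatment to the local physician and national guidance, and section 13.2.1 itself says that many patients are likely to have to pay at least part of the cost.

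Two things are at stake. The mitigation offered for the main risk is not available to Stratum B as the protocol is otherwise written. And the claim that cure stays above 90% under conservative assumptions draws on a re-treatment gain that 43 participants cannot receive.

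**Working it through.** **Who is covered.** Stratum A has 60 participants and Stratum B 43, 103 in all (sections 3.3 and 9.1). Stratum B is 43/103 = 41.7%.

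**Could the section 13.2.1 sentence be meant for Stratum A only?** Section 9.1 speaks of shortened therapy in both strata, and section 13.2.1 itself describes a 12-week course as shortened. The risk being answered therefore includes Stratum B, and the conclusion is drawn for everyone included in the study.

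**Inputs for the cure rate.**

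- First-line cure p: 90% is the target and 70% the unacceptably low rate, in both strata (section 9.1).
- Re-treatment success r: section 13.2.1 cites more than 90% and gives no value for a conservative estimate. I take 0.7 to 0.9 as an assumed range.
- Loss to follow-up is ignored.

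**Formulas, with the same p in both strata.**

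- All re-treated: p + (1 − p)r.
- Mild disease only: [60(p + (1 − p)r) + 43p]/103 = p + (60/103)(1 − p)r.

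**The protocol's own statement.** It shows no derivation, so only the inequality can be checked. With everyone re-treated and p = 0.90, overall cure is 0.90 + 0.10r, which is 97.0% at r = 0.7 and 99.0% at r = 0.9. At p = 0.70 it is 0.70 + 0.30r, or 91.0% to 97.0%. Under universal re-treatment, more than 90% is therefore reproduced even at the unacceptable first-line rate.

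**With re-treatment in mild disease only.**

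| First-line cure, both strata | Overall, r = 0.7 | Overall, r = 0.9 | Stratum B alone |
| --- | --- | --- | --- |
| 90% | 94.1% | 95.2% | 90% |
| 80% | 88.2% | 90.5% | 80% |
| 70% | 82.2% | 85.7% | 70% |

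For example, at p = 0.70 and r = 0.9: 0.70 + (60/103)(0.30)(0.9) = 0.70 + 0.157 = 0.857.

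**Break-even.** At r = 0.9, overall cure reaches 90% when p + 0.524(1 − p) = 0.90, so p = 0.376/0.476 = 0.79.

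**Stratum B from the background data.** Section 1, on genotype 6, prints 92% beside a count of 52/59 for 12 weeks of treatment in cirrhosis. But 52/59 = 88.1%. The source is not available to settle which is right, so the range is 88% to 92%.

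**The case against.** A reader might infer that the figure of more than 90% is false. The documents do not support that. The statement is conservative about re-treatment success, not about first-line cure, and its denominator is the whole study. Tested that way, with 90% first-line cure in both strata and mild-only re-treatment, overall cure is 0.90 + 0.058r, which exceeds 90% for any r above zero. Putting 52/59 in for Stratum B and keeping 90% in Stratum A, first-line cure is (54 + 37.9)/103 = 89.2%, and the total passes 90% once r exceeds about 0.13. The failing case at 70% is the rate the protocol calls unacceptable, not the one it expects.

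A reader might also infer that the promised benefit fails for 42% of participants. That goes too far. The protocol gives no rate by stratum, and at the target the Stratum B shortfall is only the difference between 90% and more than 90%. The background figure could lie on either side of 90%. It also describes 12 weeks of treatment, whereas Stratum B participants without suppression by day 14 receive 24.

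Two further points are fair. The opening benefit sentence does not mention re-treatment; only the closing sentence of that argument makes the link. And because the conduct sections agree with one another, staff are unlikely to act on the ethics sentence against all of them.

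These objections limit the size of the problem. They do not remove the contradiction, since nothing in section 13.2.1 restricts re-treatment to mild disease.

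**Conclusion.** The contradiction stands. Section 13.2.1 promises re-treatment to all not cured, while every section that governs conduct confines it to Stratum A, leaving 43 of 103 participants without it inside the protocol.

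The effect on the cure statement is narrower. At the 90% first-line target it remains true study-wide. What it loses is its stated basis for Stratum B, which gets no re-treatment gain, and its robustness. At r = 0.9, first-line cure below about 79% in both strata takes the overall figure under 90%, whereas universal re-treatment would hold it above 90% even at 70%. These figures rest on equal first-line cure in the two strata, the assumed range for r, and no loss to follow-up.

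The primary endpoint concerns first treatment only, so it, the sample size and the primary analysis are unaffected. The point matters for participant protection and for the benefit-risk case put to ethics committees.

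**What to change.** Reconcile section 13.2.1 with the trial summary, sections 2.2, 5, 5.1, 5.2, 6.2 and 13.2.4, and Appendix II, so that all name the same participants as eligible for re-treatment. Which participants those are is for the investigators to decide. Then reword the benefit statement in sections 1 and 13.2.1 to match, saying that any gain from re-treatment applies only to those eligible. Correct the mismatched count and percentage in section 1 if that figure is used as support. Check whether the participant information, which was not available here, repeats the claim.

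If re-treatment stays limited to mild disease, the cost is protocol wording and a slightly less favourable statement for Stratum B. If it is meant for everyone, the funding, the assessment schedule and the combined-cure endpoint would also have to change.
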